### Analysis of Efficacy

The final treatment evaluation will be the primary evaluation for all the primary and secondary efficacy variables. The double-blind treatment starts from the first dose of study drug, until the last dose of study drug. PPS and FAS are used for the analysis of efficacy. The analysis of PPS is based on the observed data. Unless otherwise specified, LOCF (last observation carried forward) and the observed data will be used for analysis of FAS.

The missing items of observations on the efficacy scale will be processed as described below: if up to 20% of the items are missing on one scale, the total score can be derived by multiplying the average of the available items by the total number of items. If more than 20% of the items are missing, the total score on this scale will be considered as missing. The missing total scores will be imputed using the LOCF method. For observed case (OC) analysis, the missing total scores will not be imputed. The baseline score will not be used to carry forward.

In the statistical model using study site as one independent variable the site with small number of subjects may be pooled. The anlaysis will be performed after the sites were pooled. The rules of pooled site will be provided in the statistical analysis plan, if necessary. In addition, this study is one exploratory analysis, and no adjustment of multiple tests will be carried out.

1. Analysis of the primary endpoints

The primary endpoint is the change in the total score of HAM-D_17_ scale from baseline at the final treatment evaluation, and the statistics including the number of subjects, mean, standard deviation, median, minimum and maximum will be calculated.

This is one dose-effect exploratory study, α for type I error is set as 0.1.

In the exploratory analysis of efficacy in each dose group, the mean plots for the efficacy endpointover time will be created firstly (visit time as the x axis, the mean HAM-D_17_ scale in each group as the y axis), as to observe the trend of change in the therapeutic effect over time in each dose group, and repeated measure analysis of variance (time as intragroup factor, treatment group as intergroup factor) will be used to explore the statistical significance among the doses; secondly, the mean plots for the efficacy endpoint among dose will be created (dose as the x axis, the mean HAM-D_17_ scale at the end of Week 6 as the y axis), and ANCOVA model is used to compare the change in the total score of HAM-D_17_ scale from baseline at the end of Week 6 between treatment groups, using total score of HAM-D_17_ at baseline as covariate, treatment group and site as fixed effect, as to explore of the relationship between efficacy and dose (linear growth, exponential growth or "S" growth).

1. Analysis of the secondary endpoints

The scores on each scale will be summarized using the number of subjects, mean, standard deviation, median, minimum, maximum and interquartile range by visit; the number of subjects and percentage will be used for the response rate and remission rate by visit. The analysis method for each secondary endpoint variable is as below:

CGI-I and CGI-S scale: ANOVA will be used for CGI-I, the model will be include treatment group and site as factors; ANCOVA will be used for CGI-S, the model considers the change from baseline as dependent variable, treatment group and site as fixed fators, and baseline of CGI-S as covariate variable.

HAMA and VAS-PI: ANCOVA model will be used to evaluate the change from baseline in the total score of HAMA scales, psychological anxiety score on HAMA scale, somatic anxiety score on HAMA scale and change in each subcomponent of VAS-PI at each time point, the model factors are treatment group and site, the corresponding baseline score is the covariate.

HAM-D_17_ response rate: HAM-D_17_ responder is defined as the subject with HAM-D_17_ score reduced by ≥50% from baseline. Cochran-Maenszel-Haensel test (corrected by site) will be used to analyze the response rate at each time point.

HAM-D_17_ remission rate: HAM-D_17_ remission rate is defined as the percentage of subjects with HAM-D_17_total score ≤7. Cochran-Haenszel test (corrected by site) will be used to analyze HAM-D_17_ remission rate at each time point.

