| --- | --- |
| **Investigational product** | Ansofaxine Hydrochloride Sustained-release Tablets |
| **Trial title:** | A Multicenter, Randomized, Double-Blind, Placebo-controlled, Dose-finding Clinical Trial to Preliminarily Evaluate the Efficacy and Safety of Ansufaxine Extended-release Tablets for the Treatment of Major Depressive Disorder (MDD) |
| **Objectives** | Primary objective:  To find the optimal dose of Ansufaxine extended-release tablets in the treatment of MDD.  Secondary objective:  To evaluate the preliminary efficacy and safety of Ansufaxine extended-release tablets for the treatment of MDD, thereby providing a basis for the determination of study design and dosing regimen for a phase 2I clinical trial. |
| **Subject Population** | Patients aged 18~65 years who meet DSM-IV-TR diagnostic criteria for major depressive disorder |
| **Number of subjects** | 5 groups, 52 subjects/group, a total of 260 subjects |
| **Study Methods** | Multicenter, randomized, double-blind, placebo parallel controlled, dose exploratory |
| **Investigational product** | 1. Study drug: Ansofaxine Hydrochloride Extended Release Tablet, specification 40mg, researched, developed and provided by Shandong Luye Pharmaceutical Co., Ltd. 2. Control drug: Simulator for Ansofaxine Hydrochloride Extended-release Tablet (placebo), researched, developed and provided by Shandong Luye Pharmaceutical Co., Ltd. |
| **Group and**  **Dosage and administration** | 1. Trial Grouping:   260 patients with major depressive disorder who meet the enrollment criteria will be randomized to 4 study drug dose groups of and 1 placebo group, i.e., 52 patients each group.   1. Dosage and administration:   Wash-out period: placebo two tablets, once per day, administered under fasted state or after meal at a relatively fixed time in the morning, for consecutive one week.  Treatment period: Ansofaxine Hydrochloride Extended Release Tablet 40mg, 80mg, 120mg, 160mg or placebo orally, once per day, administered under fasted state or after meal at a relatively fixed time in the morning, for consecutive 6 weeks. |
| **Course of therapy** | A total of 8 weeks, including a screening/wash-out period of two weeks and treatment period of 6 weeks. |
| **Visit frequency** | Follow-up at screening, baseline (Day 0), 1, 2, 4 and 6 weeks after administration. |

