| **Statistical analyses** | To evaluate the LY03005 extended-release tablets effect compared to placebo on change from baseline in the HAM-D17 total score at end of week 6 by using analysis of covariance (ANCOVA) model, statistical tests were conducted using two-sided test and the difference was considered statistically significant (unless otherwise specified) when P value was ≤ 0.10. Adjustment was not made when using multiple tests. Intergroup differences on change from baseline in the HAM-D17 total score were compared using ANCOVA, including the HAM-D17 total score at baseline as a covariate, and adjusted by site effect. Difference of LSMEANs compared to placebo group and associated 90% Tukey-Kramer-adjusted confidence intervals will be tabulated.  The type and frequency of adverse events and relationship with the investigational drug would be summarized. Subjects discontinued the study due to AEs and those with severe or serious AEs were noted.  The shift tables will be used for the laboratory tests, ECG findings, physical examination (clinical significance will be based on the investigator’s judgment). Abnormal findings of clinical significance were listed.  Changes in the vital signs from baseline at each visit were described and descriptive statistics were calculated, which include the number of subjects, mean, standard deviation, median, minimum and maximum. Paired t-test was used to analysis the difference between post-treatment and baseline in the same treatment group. The differences of change from baseline between treatments groups were analyzed by using ANCOVA or rank sum test. |

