## Sample size calculation

This is one phase 2 dose-exploratory study, according to the requirements of CFDA drug regulatory regulationsat, at least 200 valid cases need to be completed, and considering a (20-30)% fall-off rate, a total of 260 cases are expected to be enrolled in consideration of the possible drop-out rate of 30% during the study, and 1:1:1:1:1 randomized to Ansofaxine Hydrochloride Extended Release Tablet 40, 80, 120 and 160 mg dose groups or placebo group, there will be at least 52 screening eligible cases in each group.

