## Randomization method

MagMin minimized dynamic randomization system (<http://rct.fmmukq.com>) is used for dynamic randomization. The randomized algorithm is Pocock & Simon. After verifying that the patient is eligible per inclusion criteria and exclusion criteria, the Investigator will log in the MagMin randomization system using the account and password and get the assignment of unique randomization number and drug number for the patient. Eligible patients will be randomized 1:1:1:1:1 to receive LY03005 40mg/day, 80mg/day, 120mg/day, 160mg/day or placebo, respectively. The baseline HAM-D_17_, gender and age score will be used as important prognostic factors for baseline balancing across groups. Within each randomization, patients will be stratified for:

- HAM-D17 total score at baseline (20-30, 31-40, ≥41)
- Gender (Male, Female)
- Age, years (18-30, 31-40, 41-50, 51-65)

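### The repeated-measures ANOVA meant to show significance among the doses has no baseline or site term, and its treatment-group effect, if read, tests a visit average rather than Week-6 change (minor)

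*Protocol*

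**What the plan says.** Section 11.2, Analysis of Efficacy, defines the endpoint: "The primary endpoint is the change in the total score of HAM-D_17_ scale from baseline at the final treatment evaluation". It then describes two analyses of it.

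- The first begins with a plot over visit time, with "the mean HAM-D_17_ scale in each group as the y axis", so it shows the score and not the change. After the plot, "repeated measure analysis of variance (time as intragroup factor, treatment group as intergroup factor) will be used to explore the statistical significance among the doses". The only factors named are time and treatment group.
- The second is an ANCOVA of the Week-6 change, with baseline HAM-D17 as covariate and treatment group and site as fixed effects. It is used to compare the groups and to explore the shape of the dose relationship.

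The statistical part of the Abstract gives only the Week-6 ANCOVA for the HAM-D17 comparison with placebo. The level is fixed: "α for type I error is set as 0.1". The section calls the study exploratory and makes no multiplicity adjustment.

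For the repeated-measures model, the protocol does not say which effect is tested, whether the response is the score or the change, or whether baseline is a level of time.

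**The concern.** The primary objective is to find the optimal dose, and the protocol gives the question of significance among the doses to the repeated-measures ANOVA. In that model the test of the treatment-group factor has its own null hypothesis: the score averaged equally over the visits is the same in every arm. The average includes Weeks 1 and 2. If baseline is a level of time, it also includes a visit at which randomisation makes the arms alike. Neither matches the endpoint, which is the change at the final evaluation.

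The model also leaves between-patient differences in baseline severity, and differences between sites, in the error term. The ANCOVA beside it removes both.

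If the doses separate from placebo gradually, the repeated-measures result could be non-significant while the Week-6 ANCOVA is significant. The report would then hold two answers on the doses, with no rule for which one governs.

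**Working it through.** **1. Inputs from the protocol.** "5 groups, 52 subjects/group, a total of 260 subjects"; equal allocation ("Eligible patients will be randomized 1:1:1:1:1 to receive LY03005"); level 0.10; HAM-D17 at baseline and Weeks 1, 2, 4 and 6. The Abstract adds that "statistical tests were conducted using two-sided test", but the five-group tests here are overall F tests. The only design figure is the sample size, and it reproduces: "at least 200 valid cases need to be completed", and 200 × 1.30 = 260 = 5 × 52. No power is stated, so none can be reproduced.

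**2. Assumed inputs (not in the protocol).**
- SDs of 3.5, 5, 6, 7 and 7.5 from baseline to Week 6.
- Baseline-to-later correlation 0.35. Correlation among later visits 0.5 or 0.7 (exchangeable), or decaying at 0.8 per two weeks.
- Largest Week-6 difference 3 or 4 points, with a linear or plateau dose response.
- Share of the Week-6 effect present at baseline and Weeks 1, 2, 4 and 6: early 0/50/70/90/100%, steady 0/25/50/75/100%, late 0/0/20/60/100%.
- Complete data and no site effect, so the missing site term is not sized here.

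**3. Formula.** The noncentrality of the overall F test is λ = n f² Σ(δⱼ − δ̄)² / V. Here n = 52, δⱼ are the Week-6 differences, f is the share of the Week-6 effect that the tested quantity carries, and V is its between-patient variance.

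**4. One case in full:** 3 points, linear, steady separation, exchangeable 0.7.
- δ = 0, 0.75, 1.5, 2.25, 3, so Σ(δⱼ − δ̄)² = 5.625 and 52 × 5.625 = 292.5.
- Later visits: the variances sum to 25 + 36 + 49 + 56.25 = 166.25 and the SDs sum to 25.5. The variance of the four-visit sum is 166.25 + 0.7 × (25.5² − 166.25) = 505.05.
- Four-visit mean: V = 505.05/16 = 31.57.
- Five-visit mean: V = (505.05 + 12.25 + 2 × 0.35 × 3.5 × 25.5)/25 = 23.19.
- Mean change: V = 31.57 + 12.25 − 2 × 0.35 × 3.5 × 25.5/4 = 28.20.
- Four-visit mean with baseline as covariate: V = 31.57 − (0.35 × 25.5/4)² = 26.59.
- Week-6 ANCOVA: V = 56.25 × (1 − 0.35²) = 49.36.

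| Test | f | V | λ | Power, formula | Power, simulated |
|---|---|---|---|---|---|
| Week-6 ANCOVA | 1 | 49.36 | 5.93 | 59% | 58% |
| Treatment effect, five visits, score | 0.50 | 23.19 | 3.15 | 37% | 38% |
| Treatment effect, four visits, score | 0.625 | 31.57 | 3.62 | 41% | 41% |
| Treatment effect, four visits, change | 0.625 | 28.20 | 4.05 | 44% | 42% |
| Four-visit average, baseline as covariate | 0.625 | 26.59 | 4.30 | 46% | not run |

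The degrees of freedom are 4 and 255, or 254 with a covariate. For the five-visit test, late separation gives f = 0.36, λ = 1.63 and 24% power; early separation gives f = 0.62, λ = 4.85 and 51%.

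**5. All 36 scenarios (600 simulated trials each; error about 2 points on each power).** Week-6 ANCOVA power was 55–93%. Points lost against it (a minus sign is a gain):

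| Test read | Early | Steady | Late |
|---|---|---|---|
| Treatment effect, five visits, score | −3 to 11 | 16 to 30 | 32 to 56 |
| Treatment effect, four visits, score | −9 to 5 | 8 to 23 | 30 to 51 |
| Treatment effect, four visits, change | −15 to 1 | 3 to 18 | 28 to 45 |
| Group-by-time, baseline a level, Greenhouse-Geisser | −1 to 10 | −2 to 11 | −9 to 1 |

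Group-by-time on the four later visits only loses 9–36 points with steady separation.

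**6. Other assumed inputs.**
- SDs rising from 3.5 to 7.0, AR(1) correlation 0.6–0.8, onset 0/15/35/70/100% and Week-6 gains of 1.5/3/3/3 points: ANCOVA 71–78%; treatment effect 39–50% with baseline as a level and 46–56% without.
- A further AR(1) set: ANCOVA 69–79% against 28–52% for the unadjusted treatment effect with gradual or slow onset; from a 23-point loss to a 19-point gain with early onset. Adding baseline as covariate to the post-baseline average raised power by 5–23 points in every scenario.

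**The case against.** The strongest reply is that the Week-6 dose effect already has its own test. The ANCOVA sits in the same part of section 11.2, is the only HAM-D17 comparison with placebo in the Abstract, and matches the primary evaluation. The repeated-measures analysis adds a look across visits in an exploratory study, and no decision rule rests on it. This stands, and it limits the severity.

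Four stronger readings are tempting, and the protocol does not support them.

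- *The analysis necessarily tests the visit average.* The effect to be read is not named. The sentence follows a plot of the trend over time, so group-by-time is a natural reading too. With baseline as a level, that test has nearly the power of the ANCOVA.
- *The trial loses a fixed 20 to 40 power points.* No effect size, SD, correlation or onset is given, so no such figure can be derived. The background section expects a rapid onset. That is a hope, not evidence, but it points to the case in which the loss is small or reversed.
- *The false-positive rate exceeds 0.10.* In simulation an uncorrected group-by-time test rejected in 13–15% of trials with no effect, against 9–11% when corrected. The protocol does not say the test is uncorrected, and that detail may stand in the statistical analysis plan.
- *The primary comparison is compromised.* It is not; the ANCOVA is unaffected.

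What remains is not a detail left for later. The protocol itself chooses the model, lists its factors without baseline or site, and states its purpose.

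**Conclusion.** The point holds in a limited form. The protocol ties significance among the doses to a two-factor model without baseline HAM-D17 or site. If the treatment-group effect is read, that model does not test the Week-6 change.

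Under the assumed SDs, correlations and onset profiles, the cost of that reading is roughly 15 to 50 points of power against the Week-6 ANCOVA when separation is gradual or slow. The full grid runs from 3 points (change scores, steady) to 56 points (scores with baseline as a level, late). With early onset the result runs from a moderate loss to a gain. If group-by-time is read with baseline as a level, the difference is within about 11 points either way.

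The end-of-treatment comparison is not lost. The consequence is a weaker and possibly conflicting second answer on the doses, which is of minor severity in an exploratory trial.

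**What to change.** In section 11.2, replace the repeated-measures ANOVA with a longitudinal model of change from baseline in HAM-D17 at Weeks 1, 2, 4 and 6. Include baseline HAM-D17, site, treatment, visit and treatment-by-visit, with an unstructured covariance. Do not make baseline a level of the response. State that inference among the doses rests on the Week-6 dose-versus-placebo contrasts, consistent with the ANCOVA, and that the profile over visits is supportive.

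The cost is one sentence and a different model call, with no new data or patients. A four-visit unstructured covariance has 4 × 5/2 = 10 parameters, which 260 patients can support. One consequence should be written down: the model uses observed visits, while the full analysis set is imputed by LOCF unless otherwise specified. With dropout, the Week-6 contrasts from the model and from the ANCOVA will not agree exactly, so the text should say which one governs.

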## Dose adjustment

Change the dosage is not allowed in the clinical trial. The subjects may be suspended if subjects experience adverse events and was agreed to by the investigator, the subjects will get other treatment based on inverstigator’s judgement.

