### Analysis set of clinical trial

The analysis set defined for this study is as below:

1. Full analysis set (FAS)

It includes all the randomized subjects who were administrated at least 1 dose of double-blind study drug and had primary efficacy evaluation at baseline and at least one primary efficacy evaluation after the first dose of double-blind treatment. Unless otherwise specified, LOCF (last observation carried forward) will be used for the missing value imputation in the FAS.

FAS is the primary analysis data set for this trial.

1. Per protocol set (PPS)

It includes all the subjects who completed visit 6 and have no major protocol deviation.

1. Safety set (SS)

It includes all the subjects who were randomized and administrated at least one dose of the double-blind study drug. Subjects who were dispensed study drug but did not administrate any study drug will not included in SS.

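### Dosed patients with no post-dose HAM-D17 are in no response or remission denominator, so an arm that loses more patients before any rating can look better than it is

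*Protocol*

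**What the plan says.** Protocol 11.2, Analysis of Efficacy, summarises the two binary endpoints as follows: "the number of subjects and percentage will be used for the response rate and remission rate by visit". That sentence names no denominator. Both endpoints are then tested at each time point with a site-adjusted Cochran-Mantel-Haenszel type test. The definitions (at least a 50% reduction, and a total of 7 or less) do not say how a patient without a score is counted.

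The denominator comes from the surrounding rules:

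- **Sets.** "PPS and FAS are used for the analysis of efficacy". No all-randomised or all-dosed set is used for efficacy. In the subsection on analysis sets, "FAS is the primary analysis data set for this trial".
- **Entry to the FAS.** Besides one dose, the patient must have "had primary efficacy evaluation at baseline and at least one primary efficacy evaluation after the first dose of double-blind treatment".
- **Missing data.** "LOCF (last observation carried forward) and the observed data will be used for analysis of FAS". In addition, "For observed case (OC) analysis, the missing total scores will not be imputed", and baseline scores may not be carried forward.
- **PPS.** Visit 6 completers without a major deviation.
- **Early leavers.** Note 2 to the flow chart in section 7, the premature withdrawal visit in 7.3, and section 8.2 ask for the Week 6 assessments, which include HAM-D17, at termination. Section 7.3 asks for this only where it can be done.

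**The concern.** For a yes/no endpoint, a reader takes the percentage to mean the share of treated patients who respond. Under these rules it is the share of those who were rated (FAS) or who stayed (observed cases, PPS). A patient who takes a few doses, stops and is never rated is neither a success nor a failure. That patient disappears from the table and from the test.

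The trial's primary objective is to find the optimal dose, so the comparison between arms matters. Section 4.6 allows for 20 to 30% drop-out. The fixed dose starts on Day 1, and under 6.5 "Change the dosage is not allowed in the clinical trial", so intolerance cannot be met by a lower dose. In the multiple-dose phase I study described in section 1, the common related events were nausea, vomiting and diarrhoea. Early loss that rises with dose is therefore plausible, although nothing in the protocol shows that it will occur.

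**Working it through.** **Who is lost from which denominator**

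| Patient | FAS-LOCF | FAS observed, Week 6 | PPS |
|---|---|---|---|
| Dosed, no post-dose HAM-D17 | out | out | out |
| Dosed, rated after dosing (including at termination), no Week 6 score | in, last score | out | out |
| Completed Visit 6, no major deviation | in | in | in |

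The first row follows from the FAS condition, "at least one primary efficacy evaluation after the first dose of double-blind treatment", together with the bar on carrying baseline forward. The first scheduled post-dose rating is Visit 3, day 7 ± 1.

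**Inputs from the protocol**

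- Patients per arm: 260 / 5 = 52.
- Drop-out up to 30%: 52 × 0.30 = 15.6, about 16 per arm.
- The protocol states no response rate, no remission rate and no drop-out by arm or by time, so there is no figure of its own to reproduce. All responder and loss counts below are assumptions.

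**One arm.** Take r = 20 responders among 52 dosed, with none of those lost a responder. The rate over all dosed patients is r/52 = 38.5%. The rate the plan would report is r/(52 − lost).

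- 1 never rated: 20/51 = 39.2% (+0.8 points)
- 3 never rated: 20/49 = 40.8% (+2.4)
- 5 never rated: 20/47 = 42.6% (+4.1)
- 16 without a Week 6 score, observed cases: 20/36 = 55.6% (+17.1)

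If r runs from 10 to 26, the inflation is +1.2 to +3.1 points with 3 lost and +8.5 to +22.2 points with 16 lost.

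**Two arms with the same true 20/52**

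- FAS-LOCF, 1 v 3 never rated: 39.2% v 40.8%, a false difference of 1.6 points.
- FAS-LOCF, 1 v 5 never rated: 39.2% v 42.6%, a false difference of 3.3 points (unrounded rates).
- Observed cases, 5 v 16 lost: 42.6% v 55.6%, a false difference of 13.0 points.

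**Two arms that truly differ, FAS-LOCF.** Assume 35% of rated placebo patients and 50% of rated high-dose patients respond, with 1 of 52 never rated on placebo. The FAS difference is 50 − 35 = 15.0 points. Over all dosed patients it is:

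- 3 of 52 never rated on the high dose: 0.50 × 49/52 − 0.35 × 51/52 = 12.8 points (shift 2.2)
- 6 of 52 never rated on the high dose: 0.50 × 46/52 − 0.35 × 51/52 = 9.9 points (shift 5.1)

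The observed-case figures assume that a termination rating is not counted as a Week 6 score. The flow chart puts Visit 6 and termination in one column. If such ratings are counted as Week 6, fewer patients are lost and the distortion is smaller.

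**The case against.** A reader might infer that early leavers in general fall out of the denominator. The documents do not support that. The FAS is the primary set, LOCF is its default, and the final treatment evaluation is primary for all efficacy variables. A patient who leaves after any post-dose rating is kept with the last score. A patient who stops on Day 3 can still enter the FAS if the termination assessment is made.

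A reader might also infer that the doses will be ranked wrongly. Suppose 80 mg loses 11 of 52 with 21 responders, and 160 mg loses 20 of 52 with 19. The observed rates are 21/41 = 51.2% v 19/32 = 59.4%, while over all dosed patients they are 40.4% v 36.5%. That reversal belongs to the observed-case table alone, and a loss of 20/52 (38%) exceeds the planned 30%. Under FAS-LOCF, with every leaver rated once and none responding, the rates are 21/52 = 40.4% v 19/52 = 36.5%, so the order is kept. With 1 v 5 never rated they are 41.2% v 40.4%, still in order. Only at 1 v 6 do they tie (41.2% v 41.3%). Smaller losses can also reverse the observed-case order: 20/44 = 45.5% v 18/36 = 50.0%, against 38.5% v 34.6% of dosed. With 1 v 5 never rated, the LOCF rates in that example keep their order (39.2% v 38.3%).

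Dose-related loss is not documented either. Section 1 reports good tolerability at 40 to 160 mg/day over 7 days, roughly the window before the first rating, and placebo patients may leave for lack of effect. These are secondary endpoints in an exploratory trial whose dose-response analysis rests on HAM-D17 means. All of this stands and limits the size of the point.

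The argument that this is only detail for the statistical analysis plan does not stand. The sets, the post-dose condition and the bar on baseline carry-forward are fixed in the protocol, and together they exclude the never-rated from every efficacy analysis.

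**Conclusion.** The point holds in limited form. No planned response or remission rate includes a dosed patient who was never rated after dosing, and the observed-case and PPS rates also omit everyone without a Week 6 score.

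On assumed counts, the distortion between arms is about 2 to 5 points in the primary FAS-LOCF analysis (1 v 3 to 6 of 52 never rated) and about 13 points under observed cases (5 v 16 of 52 lost, with equal true rates). It favours an arm only if that arm loses more patients and those lost are mostly non-responders. The protocol gives no drop-out by arm, so neither the size nor the direction can be fixed in advance. The change is worth making because the rates may inform the choice of dose and the correction needs no new data.

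**What to change.** In 11.2, Analysis of Efficacy:

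- Calculate HAM-D17 response and remission at the final evaluation over all randomised patients who took at least one dose (the Safety Set population, analysed as randomised). Count patients with no post-dose HAM-D17 as non-responders and non-remitters. Keep LOCF for those with a post-dose score.
- Add a sensitivity table at Week 6 that counts every patient without a Week 6 score as a failure. This should not be the main analysis, because applied visit by visit it would turn one missed visit into a non-response even in a patient who responded before and after.
- Keep the FAS, observed-case and PPS rates as supportive.
- Report the number of patients per arm with no post-dose HAM-D17.
- Make clear that the third elimination criterion in 5.3 (no efficacy or safety record after baseline) does not take a dosed patient out of this denominator.

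The cost is a few sentences and one more table. The rates become slightly lower wherever patients go unrated: in the example with 20 responders, by 0.8 points with 1 never rated and 4.1 points with 5. The denominator will also differ slightly from that of the primary endpoint.
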